# Dose reduction of the new generation biologics (IL-17 and IL-23 inhibitors) in psoriasis: study protocol for an international, pragmatic, multicenter, randomized, controlled, non-inferiority study—the BeNeBio study

**DOI:** 10.1186/s13063-021-05681-z

**Published:** 2021-10-16

**Keywords:** Psoriasis, Dose reduction, Biologics, Non-inferiority, IL-17 inhibitors, IL-23 inhibitors, Therapy

## Abstract

**Background:**

Psoriasis is a chronic immune-mediated inflammatory skin disease for which biologics are effective treatments. Dose reduction (DR) of the first generation biologics seems a promising way for more efficient use of expensive biologics. A substantial part of patients on tumor necrosis factor (TNF)-alfa inhibitors and ustekinumab could successfully lower their dose, after following a tightly controlled DR strategy. The objective of this study is to assess whether controlled DR of interleukin (IL)-17 and IL-23 inhibitors in psoriasis patients with low disease activity is non-inferior (NI) to usual care (UC).

**Methods:**

This is an international, prospective, multicenter, pragmatic, randomized, non-inferiority trial. A total of 244 patients with stable low disease activity (Psoriasis Area and Severity Index (PASI) ≤ 5) for at least 6 months and using secukinumab, ixekizumab, brodalumab, guselkumab, risankizumab, or tildrakizumab in the standard dose, together with stable low disease activity, defined as a PASI ≤ 5 and Dermatology Life Quality Index (DLQI) ≤ 5 at the moment of inclusion, will be randomized 2:1 to DR or UC. In the DR group, dosing intervals will be prolonged stepwise to achieve 66% and 50% of the original dose. Disease activity is monitored every 3 months by PASI and DLQI. In case of disease flare (i.e., PASI and/or DLQI increase), treatment is adjusted to the previous effective dose. The primary outcome is the incidence proportion of persistent flares (PASI > 5 for ≥ 3 months), which will be compared between arms. Secondary outcomes include proportion of patients with successful DR, (course of) PASI and DLQI, serious adverse events (SAEs), health-related quality of life, costs, and pharmacokinetic profile. Outcomes of DR will be compared to UC.

**Discussion:**

With this study, we aim to assess whether DR of IL-17 and IL-23 inhibiting biologics can be achieved for psoriasis patients with low disease activity, without losing disease control. Reducing the dose may lead to more efficient use of biologics.

**Trial registration:**

ClinicalTrials.govNCT04340076. Registered on April 9 2020.

**Supplementary Information:**

The online version contains supplementary material available at 10.1186/s13063-021-05681-z.

## Introduction

### Background

Psoriasis is a chronic, immune-mediated skin disease, which is associated with important comorbidities such as cardiovascular disease and psoriatic arthritis. Disease-related quality of life impairment is large in patients with moderate-to-severe psoriasis [1]. Biologics are effective treatments which have enlarged treatment options for psoriasis patients in the past decades. Biologics block specific cytokines (tumor necrosis factor-alpha (TNFα), interleukin (IL)-12, IL-23, or IL-17) in the psoriasis pathogenesis pathway. The very long-term safety profile is yet to be established. Besides their effectiveness, biologics are expensive and impose a high burden on national healthcare expenditures [2]. Effective and efficient use of biologics is therefore warranted, including the optimal dose for the individual patient.

A new generation of biologics entered the market in recent years: IL-17 inhibitors (IL-17i) (secukinumab, ixekizumab, and brodalumab) and IL-23 inhibitors (IL-23i) (guselkumab, risankizumab, and tildrakizumab). Trial data are promising, with higher effectiveness rates than in first generation biologics like TNFα inhibitors or ustekinumab [3–5]. These biologics are registered in a fixed dose, although not every patient might need this standard dose. Previous research aiming to identify therapeutic windows of biologics showed for example that for adalimumab, one third of patients with good responses had drug levels outside the therapeutic window and were likely to be “overtreated” [6]. Hence, dose reduction (DR) seems a promising method to more efficiently and safely prescribe biologics. In the field of rheumatology, DR of TNFα inhibitors is comparable to continuation of the standard dose in patients with low disease activity [7]. For psoriasis, we recently conducted a randomized non-inferiority trial on DR of adalimumab, etanercept and ustekinumab in patients with stable low disease activity, which showed that in 53% of the patients, the dose was successfully lowered after 12 months [8]. Here, DR was achieved by extending the dosing interval of the biologics. Non-inferiority of DR based on Psoriasis Area and Severity Index (PASI) scores was not demonstrated, yet there was no difference regarding persistent disease flares, defined by disease activity and quality of life measures (PASI and/or Dermatology Life Quality Index (DLQI) scores > 5) during 3 months or longer. Furthermore, the DR strategy resulted in substantial cost savings [9]. Other studies indicated that DR of biologics in psoriasis patients might lead to lower cumulative drug exposure without losing clinical efficacy [10–13]. Direct translation of results from previous DR studies towards the newer biologics cannot be made, due to possible differences between drug classes. To our knowledge, literature regarding DR of IL-17i is sparse, and there are no studies yet that report on DR of IL-23i in psoriasis [14, 15].

With the first generation biologics (TNFα inhibitors), it was shown that discontinuing biologic treatment resulted in quick exacerbations of psoriasis [16]. For IL-17i and IL-23i, withdrawal is also associated with a risk of disease flare, although after retreatment with the original dose a substantial number of patients rapidly regained response [17–22]. Consequently, DR is preferred above treatment withdrawal. To prevent risk of disease flare with DR, we here propose a tightly controlled disease activity-guided strategy.

We designed a multicenter, pragmatic, randomized, controlled non-inferiority study with the aim to identify the number of psoriasis patients that maintain clinical effectiveness and quality of life with a reduced dose of IL-23 and IL-17 inhibiting biologics. We anticipate at least non-inferiority of DR compared to usual care (UC) on the basis of the incidence of persistent disease flares.

## Objectives

The aim of this study is to investigate whether disease activity-guided DR of IL-17 and IL-23 inhibiting biologics for psoriasis patients is non-inferior with regard to persistent disease flares compared to therapy with the standard dose. This translates into the following primary and secondary objectives.

### Primary objective

The primary objective is to assess if tightly controlled DR of IL-17i and IL-23i in psoriasis patients with low disease activity is non-inferior to UC with regard to the incidence proportion of persistent disease flares (PASI > 5 for ≥ 3 months) after 18 months.

### Secondary objectives

To assess the proportion of patients with successful DR after 12 and 18 months, defined as using a lower dose than the standard dose and PASI ≤ 5.To assess differences in course of disease activity (PASI) and dermatology-related quality of life (DLQI) in patients with DR versus UC in 18 months.To assess and compare absolute PASI and DLQI scores at month 12 and month 18 in patients with DR versus UC.To assess the incidence of short disease flares (PASI > 5 at one time point) after 18 months in patients with DR versus UC.To assess the time until the first persistent flare (PASI > 5 for ≥ 3 months).To identify predictors for successful DR.To count and compare the number of serious adverse events (SAE) and adverse events of special interest (AEoSI) in patients with DR versus UC. AEoSI include, but are not limited to, infections, malignancies, and joint complaints or new-onset psoriatic arthritis.To assess the pharmacokinetic profile of reduced biologics versus the standard dose.To assess if DR is cost-effective compared to UC.To assess the proportion of patients with initiation of other anti-psoriatic treatments during the study (intensive topical therapies, methotrexate, acitretin) in patients with DR versus UC.

## Methods

### Trial design

This is a multicenter, pragmatic, randomized, controlled non-inferiority trial. This trial will be conducted in 17 medical centers in Belgium and the Netherlands. A comparison will be made between an intervention group (DR) and a control group receiving UC (normal dose). In total, 244 patients will be randomized (2:1). In the intervention arm, the dose of the biologic will be reduced by means of prolongation of the intervals between two doses. We aim to determine whether administration of a reduced dose of the biologic is non-inferior compared to the normal, standard dose. Consequently, a randomized controlled non-inferiority design was chosen.

### Study setting

This study will be carried out in 18 departments of dermatology in Belgium and the Netherlands. Nine centers in the Netherlands will participate: five academic centers (Radboud University Medical Center Nijmegen, Erasmus Medical Center Rotterdam, Maastricht University Medical Center, University Medical Center Utrecht, University Medical Center Groningen) and five non-academic centers (Bravis hospital Bergen op Zoom, Catharina hospital Eindhoven, Gelre hospital Apeldoorn, Ziekenhuisgroep Twente Almelo/Hengelo, and Slingeland hospital Doetinchem). In Belgium, the participating centers include five academic centers (Ghent University Hospital, Cliniques Universitaires Saint-Luc Brussels, Centre Hospitalier Universitaire (CHU) de Liège, Erasme Hospital Brussels, University Hospital Leuven) and three non-academic centers or private practices (AZ Maria Middelares Ghent, AZ Sint-Lucas Ghent, and Dermatologie Maldegem).

Ethical approval for this study was obtained from the Medical Ethical Committee (Arnhem-Nijmegen) for the Dutch sites and from the competent authorities (FAMHP) and the Ethics Committee of University Hospital Ghent and University Ghent after consulting the Ethics Committees of each participating site in Belgium. Written informed consent will be obtained from each participant.

### Eligibility

Adult patients with plaque psoriasis who are treated with IL-17i or IL-23i in the standard, registered dose for at least 6 months, and who have stable low disease activity, are eligible. Low disease activity is defined as PASI ≤ 5 in the previous 6 months and at the moment of inclusion, together with a DLQI ≤ 5 at inclusion. In case no PASI scores are available, it should be clear from the patient record that the psoriasis was “clear” or “almost clear” in the past 6 months. A PASI ≤ 5 is chosen based on experts’ opinion and our previous DR study [8]. The DLQI score was added in order to adjust to the impact of psoriasis on the patients’ quality of life [23]. A DLQI ≤ 5 indicates mild influence on quality of life [24]. In order to establish whether good disease control is present, a combination of PASI as a clinical outcome measure and DLQI as a patient reported outcome measure will be assessed every 3 months during the study (tight control). Patients who are eligible for inclusion in this study must meet the following criteria:

### Inclusion criteria

Plaque psoriasis (primary indication for biologic).Treatment for at least 6 months with IL-23i or IL-17i in the standard dose (dose advised by the label).PASI ≤ 5 in the previous 6 months. If no PASI scores are available in the previous 6 months, it should be clear from the patient record that the psoriasis was clear or almost clear.PASI ≤ 5 at inclusion.DLQI ≤ 5 at inclusion.

### Exclusion criteria

Another indication than plaque psoriasis as the main indication for biologic use (e.g., psoriatic arthritis).Concomitant use of systemic immunosuppressants other than methotrexate or acitretin.Severe comorbidities with short life-expectancy.Presumed inability to follow the study protocol.

### Recruitment

All patients who are eligible for this study will be asked by their treating physician. They will receive oral and written information from the local investigator. The investigator will obtain written informed consent and the patient will be randomized. The dosing schedule will be explained depending on which biologic the patient uses. Patients can leave the study any time for any reason without consequences. The investigator can decide to withdraw a subject from the study for urgent medical reasons. When subjects are withdrawn from the study, they will not be replaced.

### Randomization, blinding, and treatment allocation

The investigator will enroll participants. After including the participant and obtaining written informed consent, the investigator will enter participants in a web-based randomization program (Castor). Participants will be allocated to each group (DR or UC) by this web-based randomization program (Castor) that generates block randomization (variable block size of 6, 9, 12) with a random (2:1) allocation sequence and stratified by biologic. After randomization, the randomization group is visible for the investigator and the investigator will inform the participant. Patients will be randomized 2:1 to DR or continuation of the normal dose (UC). The ratio of 2:1 is chosen to be able to include more determinants in an analysis for successful DR. Due to the pragmatic character of this trial, and due to the nature of the intervention (injections), patients and investigators will not be blinded. Patients in the DR group will receive secukinumab, ixekizumab, brodalumab, guselkumab, risankizumab, or tildrakizumab, and doses will be lowered according to the schedule as described below (Table 1). Patients in the control group will receive the normal, standard dose of secukinumab, ixekizumab, brodalumab, guselkumab, risankizumab, or tildrakizumab without interval prolongation.

**Table 1 Tab1:** Dose reduction (DR) steps per biologic

Biologic	Normal dose	First step DR	Second step DR
Secukinumab	300 mg/4 weeks	300 mg/6 weeks	300 mg/8 weeks
Ixekizumab	80 mg/4 weeks	80 mg/6 weeks	80 mg/8 weeks
Brodalumab	210 mg/2 weeks	210 mg/3 weeks	210 mg/4 weeks
Guselkumab	100 mg/8 weeks	100 mg/12 weeks	100 mg/16 weeks
Risankizumab	150 mg/12 weeks	150 mg/18 weeks	150 mg/24 weeks
Tildrakizumab	100 or 200 mg/12 weeks	100 or 200 mg/18 weeks	100 or 200 mg/24 weeks

*Abbreviations*: *DR* dose reduction, *mg* milligram

### Study groups

### Control group

Patients in the control group will continue treatment with the normal, standard dose based on the prevailing national guidelines. Treatment decisions are made at the discretion of the treating physician following these guidelines. Control visits are planned every 3 months and patients are explained to contact their physician when they experience increased disease activity. The PASI and DLQI are performed during 3-monthly outpatient clinic visits. Topical therapies and concomitant use of methotrexate or acitretin are allowed. In case of a disease flare, treatment will be adjusted. Topical and/or systemic therapy will be optimized and when required the dose of the biologic will be increased or the biologic will be switched to another agent. In case of treatment alternations, the patient will remain in the study for follow-up.

### Dose reduction group

The doses of secukinumab, ixekizumab, brodalumab, guselkumab, risankizumab, or tildrakizumab will be lowered by interval prolongation in two steps to 66% and 50% of the original dose, respectively (Table 1). The intervals of drug administration will be prolonged depending on the PASI and DLQI score (Fig. 1). DR is allowed in case of low disease activity, defined as PASI ≤ 5 and DLQI ≤ 5. First, the dose will be decreased to 66% of the normal dose of the biologic (by interval prolongation with a factor 1.5). After 3 months, if there remains low disease activity (PASI ≤ 5 and DLQI ≤ 5), the dose will be further reduced to 50% of the original dose (by doubling the original interval). When disease flare occurs (PASI > 5 and/or DLQI > 10), or when the patient is not willing to further use the lower dose, the patient will return to the previous effective dosing interval. In case of PASI ≤ 5 and DLQI > 5 but ≤ 10, it will be discussed with the patient if the reduced dose remains acceptable and can be continued or not. If possible, the patient will stay on the lowest dose. Each step will be analyzed after 3 months, or when the patient visits earlier due to complaints. In case a patient returned to the previous effective dosing interval, the dose will not be reduced again at a later time point. Topical therapies and concomitant use of methotrexate or acitretin are allowed. When there is still no disease control after reintroduction of the normal dose, treatment will be adjusted. Topical and/or systemic therapy will be optimized and, when required, the dose of the biologic will be increased or patients will switch to another agent. In case of treatment alternations, the patient will remain in the study for follow-up.

**Fig. 1 Fig1:**
[figure not shown]
Participant timeline. Patients (*n* = 244) using secukinumab, ixekizumab, brodalumab, guselkumab, risankizumab, or tildrakizumab will be randomized to dose reduction or usual care. Control visits will be scheduled every 3 months for assessment of PASI, DLQI, cost-effectiveness questionnaires (EQ-5D-5L, SF-36, iMTA MCQ, and PCQ), drug levels, and anti-drug antibodies. CEQ, Cost-Effectiveness Questionnaires; PASI, Psoriasis Area and Severity Index; DLQI, Dermatology Life Quality Index

### Procedures and outcome measures

At baseline, patient and treatment characteristics will be collected, such as sex, age, treatment history, comorbidities, and disease duration. Patients will be followed for 18 months and regular visits will be planned at baseline, month 3, 6, 9, 12, 15, and 18. An overview of interventions and assessments by study time point is presented in Table 2. If a patient has a disease flare outside the regular visits, an additional study visit will be planned. Every 3-monthly visit, PASI and DLQI scores will be retrieved, and blood samples will be drawn for determining anti-drug antibody levels and modeling drug trough levels. Also, dosage schedules, adverse events, and concomitant topical and systemic medication use will be registered. Medication dispensing records will be collected for each participant from their pharmacies. Patients will be asked to fill in patient diaries with information on medication use. Questionnaires relevant for cost-effectiveness analysis will be completed in by the patients at these visits. These include the European Quality of Life-5 Dimensions-5 Level (EQ-5D-5L) questionnaire [25], the Short Form (SF)-36 questionnaire [26], and adapted versions of the “institute for Medical Technology Assessment” (iMTA) Medical Consumption Questionnaire (MCQ) and Productivity Cost Questionnaire (PCQ) [27].

**Table 2 Tab2:**
[figure not shown]
Schedule of enrolment, interventions, and assessments by study time point

*Abbreviations*: *M* months, *PASI* Psoriasis Area and Severity Index, *DLQI* Dermatology Life Quality Index, *EQ-5D-5L* European Quality of Life-5 Dimensions-5 Level questionnaire, *SF-36* Short Form-36 questionnaire, *iMTA MCQ* institute for Medical Technology Assessment Medical Consumption Questionnaire, *PCQ* Productivity Cost Questionnaire

Our primary outcome is non-inferiority of the incidence proportion of persistent flares (PASI > 5 for ≥ 3 months) in the intervention group. If the 95% confidence interval from the difference in incidence of persistent flares in the intervention group versus control group exceeds the non-inferiority margin (15% difference in persistent flares) at 18 months of follow-up, it can be concluded that non-inferiority could not be demonstrated for DR.

Our secondary study outcomes are as follows:
Whether participants will have successful DR after 12 and 18 months, defined as using a lower dose than the normal dose and PASI ≤ 5.Psoriasis disease activity, measured with the Psoriasis Area and Severity Index (PASI) at each 3-monthly study visit. The PASI is a composite measure of erythema, scaling, induration, and extensiveness of the psoriasis plaques [28]. It results in a single score for psoriasis severity ranging from 0 to 72 with lower scores indicating lower disease activity.Dermatology-related quality of life as measured with the Dermatology Life Quality Index (DLQI) at each 3-montly study visit. The DLQI is a practical questionnaire for routine clinical use and consists of 10 questions surveying the impact of skin disease on health-related quality of life. A total sum score ranging from 0 to 30 is derived from all questions, with lower scores indicating limited impact on disease-related quality of life [23].Whether participants will have short disease flares throughout the study period (18 months), defined as a PASI > 5 at one time point.Whether other anti-psoriatic medication will be initiated in participants during the study period (18 months). Investigators will report start of other medications at every study visit.Whether participants will have serious adverse events (SAE) and adverse events of special interest (AEoSI) during the study period. AEoSI include, but are not limited to, infections, malignancies, and joint complaints or new-onset psoriatic arthritis. All adverse events reported spontaneously by the participant or observed by the investigator will be recorded in the CRF during the study period (18 months).Drug trough levels of each included drug will be measured in blood serum samples which will be collected from participants at each 3-montly time point. Serum samples will be analyzed through an enzyme-linked immunosorbent assay (ELISA) for serum drug and anti-drug antibody levels.Anti-drug antibody levels of each included drug will be measured in blood serum samples which will be collected from participants at each 3-montly time point. Serum samples will be analyzed through an enzyme-linked immunosorbent assay (ELISA) for serum drug and anti-drug antibody levels.Utilities will be derived from EuroQoL 5 Dimensions (EQ-5D-5L) questionnaires, which will be measured at each 3-montly time point. The EQ-5D-5L questionnaire consists of 5 dimensions (mobility, self-care, usual activities, pain/discomfort and anxiety/depression), and each dimension has 5 levels: no problems, slight problems, moderate problems, severe problems, and extreme problems. In addition, patients are asked to complete a visual analog scale to rate their health status at a scale of 0–100 [25]. Utility scores will be used to calculate quality-adjusted life years (QALYs) which are used to determine cost-effectiveness of DR.Health status of participants will be assessed by using the Short Form 36 (SF-36) version 2 questionnaire at every 3-monthly time point. The SF-36 consists of 36 questions regarding 8 domains of health, including physical functioning, physical role, pain, general health, vitality, social function, emotional role, and mental health [26, 29]. Scores from all domains will be summarized with differing weightings to calculate mental component scores (MCS) and physical component scores (PCS). Utilities will be derived as well from the SF-36 for sensitivity analyses, calculated based on the 12 specific SF-36 questionnaire answers included in the SF6D system.Volumes of care, as measured with the iMTA Medical Consumption Questionnaire (MCQ) at each 3-monthly time point. The iMTA MCQ measures all relevant health care related costs like outpatient visits at any medical specialist, hospitalizations, and imaging procedures [27]. Scores will be used to calculate direct medicals costs and non-medical costs.Loss of productivity and presenteeism of participants, as measured with the iMTA Productivity Cost Questionnaire (PCQ) at each 3-monthly time point. The iMTA PCQ measures patient-reported absences from paid or unpaid labor [30]. Scores will be used to calculate direct medicals costs and non-medical costs.

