
### Definition of disease flare

We defined a psoriasis flare as a PASI score > 5. A short disease flare was defined as a flare at one time point, and a persistent flare as a PASI > 5 for at least 3 months. Successful DR was defined as use of a lower biologic dose and a PASI ≤ 5. A PASI cutoff of 5 was chosen in absence of a validated definition for psoriasis flare. This cutoff was based on our previous DR trial [31], where PASI 5 was chosen based on expert opinion and on previous data that showed that patients who remain on a biologic reach average PASI scores ≤ 5 [32]. Although disease flare is based on disease activity only, quality of life measured by DLQI is incorporated in the tightly controlled DR strategy. In patients where PASI 5 reflects active disease, patients can always return to their previous effective dose or the normal dose when they experience larger impact of their psoriasis on their quality of life. Incidence of persistent flares was chosen as primary outcome to assess non-inferiority. Brief, temporary flares that improve after treatment adjustments or reintroduction of higher doses, and without large impact on overall disease control, might occur more frequent in a DR arm and are inherent to such a strategy. However, to not harm the patient, such effects should not last too long. For this reason, persistent flares are chosen as the primary outcome. PASI is used instead of Psoriasis Global Assessment (PGA) as PASI is a common used tool in Europe daily practice and in clinical trials. Assessment of PASI is standardized, whereas for PGA different scales and subtypes are used [33]. PASI has been reported to be a reliable instrument to evaluate treatment success when measured at baseline and during treatment [34].

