The strength of this study is that it will be performed in two different countries, and in various academic and non-academic centers, to improve external validity. Moreover, the real-world practice setting, flexibility of treatment schedule, and outcomes relevant to patients lead to a highly pragmatic trial of which outcomes have a high generalizability [46]. A possible limitation is the open-label design of this study, as reporting bias might occur for patient reported outcomes such as adverse events. However, as said, the aim of this pragmatic study is to provide high external validity, which would be lowered by blinding.

The focus of this study is on the strategy of DR in general. Hence, the study is powered for the total group and not per biologic. In addition, subanalyses per drug class and per biologic will be performed when appropriate.

More knowledge on DR of biologics might contribute to more efficient and effective use of biologics. The COVID19 situation has emphasized the need for more research regarding personalized dosing and the possibility of lower dosages of immunomodulatory biologics [47]. In this prospective, multicenter, randomized controlled non-inferiority trial, the possibility of DR of the newer generation biologics (IL-17i and IL-23i) will be investigated. If DR is non-inferior to UC with standard dosages, we can provide patients with more personalized treatment. This may lead to lower cumulative doses of therapy, a lower risk of side-effects, and reduction of healthcare costs.

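### Infections and joint complaints are recorded on spontaneous report or investigator observation in an open-label trial, so they may be incompletely captured, and captured differently by arm

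*Protocol article*

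**What the plan says.** Under Procedures and outcome measures, the safety item in the list of secondary outcomes gives the recording rule: "All adverse events reported spontaneously by the participant or observed by the investigator will be recorded in the CRF". The main text of that section sets the timing, at every 3-monthly visit: "Also, dosage schedules, adverse events, and concomitant topical and systemic medication use will be registered". Neither sentence says that patients are questioned in a fixed way.

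Secondary objectives names the events to be compared between arms: "AEoSI include, but are not limited to, infections, malignancies, and joint complaints or new-onset psoriatic arthritis". Statistical analyses tests serious adverse events and AEoSI between groups with Fisher's exact test and reports proportions and rate ratios.

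Four further statements bear on whether the arms are observed alike:

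- Randomization, blinding, and treatment allocation: "patients and investigators will not be blinded".
- Procedures and outcome measures, for any patient: "If a patient has a disease flare outside the regular visits, an additional study visit will be planned".
- Definition of disease flare, on brief flares: they "might occur more frequent in a DR arm and are inherent to such a strategy".
- Dose reduction group: "Each step will be analyzed after 3 months, or when the patient visits earlier due to complaints".

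The Discussion concedes that "reporting bias might occur for patient reported outcomes such as adverse events". It defends the absence of blinding on grounds of external validity and offers no mitigation for the adverse-event data.

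**The concern.** Joint pain or a minor infection since the last visit is known mainly to the patient. At a visit about the skin it may go unmentioned unless someone asks, and the investigator can observe only what is present that day. Capture may therefore be incomplete.

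Capture may also differ by arm. Everyone knows the allocation, which can change what patients volunteer and what staff look for. Extra visits add occasions to mention an event, and the article's own expectation about brief flares makes such visits plausibly more frequent in the DR arm.

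At stake is the secondary safety comparison. The Discussion hopes that lower cumulative doses will bring fewer side effects. Better capture in the DR arm could hide such a benefit or create an apparent harm, and better capture in the UC arm could do the opposite.

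**Working it through.** **What the passages fix.** The registration sentence sets when adverse events are entered, and the recording sentence sets which events qualify. Read together, they give both arms the same 3-monthly schedule but no standard question. The extra-visit rule is worded alike for both arms. Any imbalance in contacts would come from flare frequency, which the article says only might be higher in the DR arm.

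**Inputs.** Arm sizes of 162 and 82 (Power and sample size analyses) and Fisher's exact test (Statistical analyses), taken two-sided at 5%. The article gives no AEoSI risks and no capture rates, so those below are assumptions. There is no figure in the plan to reproduce.

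**Model.** Observed risk = true risk × capture probability in that arm. The probability of p < 0.05 is the sum of the two binomial probabilities over all pairs of counts for which Fisher's test rejects.

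**Step 1: equal incomplete capture.** With a true risk of 40% in both arms and 60% capture in both, the observed risk is 0.40 × 0.60 = 24% in each arm. The risk ratio stays at 1.00 and the rejection rate is 4.1%, as with full capture. There is no bias.

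Power does fall. Assume true joint complaints of 15% DR v 5% UC:

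| Capture, both arms | Observed DR v UC | Power |
|---|---|---|
| 100% | 15% v 5% | 64% |
| 80% | 12% v 4% | 50% |
| 60% | 9% v 3% | 35% |
| 40% | 6% v 2% | 19% |

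**Step 2: capture that differs by arm, with equal true risk.** UC capture is held at 60%. The expected risk ratio is DR capture / 0.60. The last three columns give the rejection rate at each true risk.

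| DR capture | Risk ratio | True risk 20% | True risk 40% | True risk 60% |
|---|---|---|---|---|
| 65% | 1.08 | 4.3% | 5.2% | 6.2% |
| 70% | 1.17 | 5.4% | 8.7% | 12.7% |
| 80% | 1.33 | 10.3% | 22.4% | 40.1% |

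The gap between the arms drives the result. With a gap of 5 percentage points the error rate stays close to nominal; with a gap of 20 points it does not.

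**Step 3: masking.** Assume a true benefit of DR, 30% v 45%. Full capture gives 62% power. With capture of 80% v 60%, the observed risks are 0.30 × 0.80 = 24% and 0.45 × 0.60 = 27%, and power is about 7%.

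**The case against.** - **The text is a condensed article.** The full protocol and the case report form are not shown, and either may prompt for infections and joint complaints. This stands as a caveat. The article does not merely stay silent, however: it states a recording rule, and that rule does not describe prompting. If prompting exists, the published sentence needs correcting.
- **Spontaneous report is not the only route.** Investigator observation is the second, registration takes place at every scheduled visit in both arms, and Oversight and monitoring requires all adverse events in the source record and the electronic system. A reader might infer that these events are under-counted as a matter of fact. The documents do not support that; they support a risk.
- **More contacts in the DR arm are inferred.** The extra-visit rule covers any patient, the Control group section tells UC patients to contact their physician when disease activity rises, and an event missed between visits can still be mentioned at the next one. This stands: the imbalance is plausible but not stated.
- **Other symmetric sources exist.** The medical consumption questionnaire, concomitant medication and pharmacy dispensing records may show treated infections or joint referrals in either arm. They would not show untreated complaints.
- **The figures are assumed.** This is true. The 22% needs a capture gap of 80% v 60%, and at 70% v 60% the figure is 9%. A reader might also infer that the safety result cannot be interpreted at all. That does not follow, since equal under-capture leaves the risk ratio intact.
- **The limitation is disclosed.** It is, but the defence offered is external validity, and a standard question in both arms costs no external validity and needs no blinding.

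**Conclusion.** The concern holds as a risk. The stated recording rule leaves infections and joint complaints dependent on being volunteered or noticed, in an unblinded trial whose DR arm may have more extra visits. Two consequences should be kept apart. Incomplete capture lowers power. Capture that differs by arm can bias the Fisher comparison, and the net direction is unknown because extra contacts and knowledge of allocation may pull in different directions.

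The size cannot be fixed from the article. At an equal true risk of 40%, the illustration runs from about 5% false differences (65% v 60% capture) through 9% (70% v 60%) to 22% (80% v 60%). The PASI-based primary outcome is not affected. Because the remedy uses visits that already take place, the change is worth making, although it concerns only a secondary comparison.

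**What to change.** In Procedures and outcome measures, both in the visit description and in the safety item of the outcome list, add one fixed yes/no question on infections and one on joint complaints, each covering the time since the last scheduled visit. Ask them at every scheduled 3-monthly visit in both arms. Anchoring recall to the last scheduled visit matters: if the window restarted at an extra visit, events reported there could drop out of the answers, mostly in the arm with more such visits.

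Keep all events in the main AEoSI analysis. Record whether each was first found at a scheduled or an extra visit, and add a sensitivity comparison based on the scheduled-visit answers. Comparing the SF-36 pain domain and the EQ-5D-5L pain/discomfort item by arm is at most a supportive check: both are already collected, but neither is specific to joints and both are unblinded self-report.

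The cost is two yes/no fields plus a flag for scheduled or extra visit in the electronic form, a short amendment, and analysis wording. No visit is added. The downsides are that more minor events will be recorded, that visits before the amendment are not covered in either arm (recruitment began in August 2020), and that patients and staff still know the allocation, so the bias is reduced but not removed.
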